**Figure 1 F1:**
[figure not shown]
**Enrolment Flowchart**. The figure illustrates how the participants are enrolled and allocated.

Eligible patients must fulfill all the following requirements: age from 20 to 85 years, a disease diagnosis meeting the definition of septic shock, use of vasopressors now and an initiation of vasopressor use within 24 hours of entering the study, use of a nasogastric tube for feeding, and informed consent obtained from either the patients or their relatives.

Exclusion criteria are an extremely poor gastrointestinal function and an inability to tolerate diet feeding, acute myocardial infarction, evidence of major bleeding, expected or scheduled surgical intervention in the subsequent one week, use of 2 or more than 2 kinds of vasopressors upon entrance into the study, and patients who have received digoxin for arrhythmia within the past one week.

The treatment for the patients with septic shock in our hospital adheres to the Surviving Sepsis Campaign: International guidelines for management of severe sepsis and septic shock 2008. Our study uses block randomization with a block size of 4 and an allocation ratio of 1:1. After enrolment, the eligible patients are either allocated to the Si-Ni-Tang group or the placebo group. The prescription of the trial drugs is 2.25 grams 4 times a day (9 grams per day) for 7 days or till shock reversal (if shock reversal occurs in less than 7 days). Shock reversal is defined as the discontinuation of norepinephrine or dopamine for at least 24 hours.

We will collect the following data from each participant: gender, age, co-morbidities, APACHE II score, predicted mortality, ICU mortality, ICU length of stay, hospital mortality, hospital length of stay, source of sepsis (pulmonary, gastrointestinal, renal or others), culture results (Gram-positive, Gram-negative or mixed) and duration of vasopressor infusion. Shock reversal and time to cessation of vasopressor use would be the primary outcome measurements.

Baseline variables will be evaluated for balance between the two groups using the Student's t-test for unpaired data for the comparison of continuous variables and the Pearson's chi-squared test to compare categorical variables.

The effect of Si-Ni-Tang treatment on time to cessation of vasopressor use is estimated, first, from Kaplan-Meier curves and log-rank test for median time, and second, from adjusted Cox proportional hazards regression models for potential confounders (age, APACHE II score at baseline, source of sepsis, co-morbidities). Corresponding hazard ratios along with their 95% confidence intervals are reported. Patients who died before cessation of vasopressor use are treated as censored. Analysis is performed on the intention to treat population.

There is no planned subgroup analysis anticipated. Only primary and secondary outcome measures will be analyzed. However, all of the variables which are found to be important predictors of shock reversal and adverse outcome will be used for stratifications for post-hoc analysis (relative risks will be estimated for the major outcomes using multivariate Poisson regression adjusting for covariates).

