Our study is being carried out somewhat like phase 2 studies in clinical trials. Phase 2 studies are set forth to evaluate the effectiveness of drugs in participants with a certain disease or condition. We assume that the mean duration of vasopressor use of the Si-Ni-Tang group is 3 hours shorter than that of the placebo group, with a standard deviation of 6.5 hours. Under the setting of alpha = .05 and power = 80%, the calculated sample size of each group is around 60. This is why we plan to enroll 120 participants.

Sepsis is an infectious disease, usually caused by bacterial infection, with systemic manifestations. Sepsis-induced hypotension is defined as a systolic blood pressure less than 90 mmHg or mean arterial pressure less than 70 mmHg. Septic shock is defined as persistent hypotension induced by sepsis, despite adequate fluid resuscitation. We plan to enroll 120 patients who have been admitted to our medical intensive care units with the diagnosis of septic shock. The flow chart of the study is illustrated as Figure 1.

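### The clock for vasopressor time has no stated start, so up to 24 hours before randomisation may enter a primary comparison that looks for a 3-hour difference

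*Protocol article*

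**What the plan says.** All of this is in the Methods/Design section of the protocol article.

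- **Eligibility:** a patient must satisfy "use of vasopressors now and an initiation of vasopressor use within 24 hours of entering the study".
- **Data collected:** the list ends with "culture results (Gram-positive, Gram-negative or mixed) and duration of vasopressor infusion". The abstract's Methods/Design paragraph has the same item. No other vasopressor time is listed.
- **Sample size:** the assumption is that the "mean duration of vasopressor use of the Si-Ni-Tang group is 3 hours shorter than that of the placebo group". The spread assumed for this variable is an SD of 6.5 h. The other settings are "Under the setting of alpha = .05 and power = 80"%, giving around 60 per group. Whether alpha is one- or two-sided is not stated.
- **Outcome:** "Shock reversal and time to cessation of vasopressor use would be the primary outcome measurements".
- **Analysis:** "The effect of Si-Ni-Tang treatment on time to cessation of vasopressor use is estimated" by Kaplan-Meier curves and a log-rank test, then by a Cox model adjusted for age, APACHE II score, source of sepsis and co-morbidities, in the intention-to-treat population.

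Nowhere does the article say whether time to cessation starts at vasopressor start, study entry, randomisation or first dose.

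**The concern.** An infusion duration, read plainly, starts when the infusion starts. Under the eligibility rule that can be up to 24 h before entry, eight times the 3 h target (24/3 = 8). Every enrolled patient is still on a vasopressor at entry, so no enrolled patient can have the event in those hours. A Kaplan-Meier or Cox analysis that starts at infusion start, without allowing for delayed entry, would count them as time at risk all the same.

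The pre-entry hours differ between patients and are fixed before treatment begins. If they are part of the outcome, they blur the order of event times between arms, weaken the hazard ratio, lengthen the median in both arms and reduce power. The Cox covariates do not include them, so the adjusted model does not recover the loss.

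The article uses a duration for collection and sample size and a time to cessation for analysis, and does not say that the two are the same variable or how they differ.

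**Working it through.** **Inputs.** From the article: difference 3 h, SD 6.5 h, alpha 0.05, power 80%, about 60 per group, allocation 1:1, entry window 24 h. Assumed, because the article gives no distribution: pre-entry time is uniform on 0 to w hours and independent of time after entry, so its variance is w²/12.

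**Step 1, the plan's own figure.** n per group = 2 × (z_alpha + z_power)² × SD² / difference².

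- One-sided: 2 × (1.645 + 0.842)² × 42.25 / 9 = 58.1, so 59. This matches the stated figure of around 60.
- Two-sided: 2 × (1.960 + 0.842)² × 42.25 / 9 = 73.7, so 74. This does not.

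Sidedness is a separate matter, so both versions are carried below.

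**Step 2, if 6.5 h is the SD of time after entry and the whole infusion is analysed.** SD = √(6.5² + w²/12). Power at 60 per group = Φ(3 / (SD × √(2/60)) − z_alpha).

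| Pre-entry spread | SD (h) | Power two-sided | Power one-sided | n per group for 80%, two- / one-sided |
|---|---|---|---|---|
| none | 6.50 | 71% | 81% | 74 / 59 |
| 0 to 6 h | 6.73 | 68.5% | 79% | 79 / 63 |
| 0 to 12 h | 7.37 | 61% | 72% | 95 / 75 |
| 0 to 24 h | 9.50 | 41% | 53% | 158 / 124 |

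Example, 0 to 24 h: SD = √(42.25 + 48) = 9.50; 3 / (9.50 × 0.1826) = 1.73; 1.73 − 1.96 = −0.23; Φ(−0.23) = 0.41.

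**Step 3, if 6.5 h is the SD of the whole infusion.** The spread before entry is then already inside it, and counting from entry removes it: SD = √(6.5² − w²/12).

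- 0 to 6 h: SD 6.26 h, power 75% two-sided, 84% one-sided.
- 0 to 12 h: SD 5.50 h, power 85% two-sided, 91% one-sided.
- 0 to 24 h: not possible under these assumptions, since 24²/12 = 48 exceeds 42.25.

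**Step 4, the planned log-rank test, by simulation.** 60 per arm, two-sided, no censoring, pre-entry time uniform over 0 to 24 h.

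- Gamma times after entry with the plan's 3 h difference and 6.5 h SD, placebo means 12, 24 and 48 h: power 58 to 60% counting from entry, 33 to 36% counting from vasopressor start.
- Exponential times after entry, true hazard ratio 1.5. Placebo mean 12 h: hazard ratio 1.42, power from about 60% to about 46%. Mean 24 h: hazard ratio 1.48, power from 58% to about 55%. Mean 48 h or more: about 1 point lost.

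An exponential time has an SD equal to its mean, so the second set shows what happens when times after entry vary more than 6.5 h: the loss shrinks quickly.

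**Step 5, chance imbalance.** With a 0 to 24 h spread, the SD before entry is 24/√12 = 6.93 h. The standard error of the between-arm difference in mean pre-entry time is 6.93 × √(2/60) = 1.26 h. A difference beyond 1.5 h, half the target, would arise in about 24% of trials. This is sampling error already counted in Step 2, not an extra bias.

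**The case against.** The article never says that the clock starts at infusion start. The infusion duration is one item in a data list. The primary outcome has another name, and randomisation is the usual origin for an intention-to-treat log-rank or Cox analysis. The full protocol or the statistical analysis plan may fix the origin, and an article need not repeat it. This stands in part. A reader might infer that pre-entry time does enter the comparison; the documents support only that it may.

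The omission argument does not dispose of the point. The article does state the variable collected and the variable powered on. Both are durations, and its own entry rule lets hours before randomisation fall inside them unless the clock is restarted.

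Three further objections stand.

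- The fall from 71% to 41% treats 6.5 h as an SD after entry. Anyone who reads the sample-size duration as starting with the infusion cannot also add the pre-entry variance on top; on that reading there is no shortfall, only power to be gained.
- A reader might infer a biased treatment effect. Pre-entry time is fixed before allocation and balanced in expectation, so neither the mean difference nor the type I error is biased.
- Treatment may last up to 7 days, so shock lasting several days is foreseen. If times after entry are that variable, little is lost.

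**Conclusion.** The point holds in a limited form. The article leaves the time origin open and words its collected and powered variables so that up to 24 h before randomisation may be included. The harm would be noise, a diluted hazard ratio and lost power.

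The range runs from about 1 percentage point (exponential times with a mean of 48 h or more) to about 30 points two-sided (71% to 41%: SD after entry 6.5 h, entry spread evenly over the full 24 h). With entry spread over 12 h and the same SD, it is about 10 points. None of these can be called the expected loss, because the article gives neither the distribution of pre-entry time nor the variable to which 6.5 h belongs. In the cases computed, counting from randomisation gives at least as much power on either reading of 6.5 h, so the change is worth making without settling that question first.

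**What to change.** - **Outcome and analysis paragraphs:** define time to cessation as running from randomisation, for all randomised patients.
- **Sample-size paragraph:** state that the 3 h difference and the 6.5 h SD refer to that post-randomisation time. If the 6.5 h came from whole-infusion data, say so and restate it.
- **Data list:** record the vasopressor start time as well as the stop time.
- **Cox model:** add vasopressor hours before randomisation to the baseline covariates.
- **Reporting:** give total infusion duration as a description only.

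The cost is wording and one baseline time that must already be known to check the 24 h criterion. No extra patients or procedures are needed.

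### The adjusted analysis of time to vasopressor cessation omits vasopressor support at entry, giving up precision that routine chart data could recover cheaply

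*Protocol article*

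**What the plan says.** All references are to the Protocol article, Methods/Design.

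- **Outcome.** "Shock reversal and time to cessation of vasopressor use would be the primary outcome measurements".
- **Eligibility.** A patient qualifies with "use of vasopressors now and an initiation of vasopressor use within 24 hours of entering the study". Patients on two or more kinds of vasopressor at entry are excluded. No limit on dose is given. The definition of shock reversal names two agents, norepinephrine and dopamine.
- **Data list.** Its only vasopressor item comes at the end: "culture results (Gram-positive, Gram-negative or mixed) and duration of vasopressor infusion". That item is the outcome.
- **Randomisation.** 1:1 in blocks of four, with no stratification factor named.
- **Analysis.** The effect on time to cessation is estimated first by Kaplan-Meier curves and a log-rank test, then by a Cox model adjusted for "potential confounders (age, APACHE II score at baseline, source of sepsis, co-morbidities". Predictors found to be important may also be used later for post-hoc stratification.
- **Sample size.** It assumes that "the mean duration of vasopressor use of the Si-Ni-Tang group is 3 hours shorter than that of the placebo group". The SD is put at 6.5 h.

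**The concern.** How much vasopressor a patient is on, which agent it is, and how long it has been running are the baseline quantities closest to how long it will still be needed. The entry rules admit a wide range: a patient on a small, falling dose late in the 24-hour window and a patient on a high, rising dose in the first hour both qualify. Blocking on order of entry equalises numbers per arm but not starting support, and the named covariates do not include it.

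At stake is efficiency. An unadjusted strong predictor leaves avoidable variation in the comparison. If entry dose is not collected, an imbalance in it can be neither shown in the baseline table nor allowed for, and the post-hoc stratification cannot use it.

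**Working it through.** **Inputs.** Difference 3 h, SD 6.5 h, alpha 0.05, power 80%, about 60 per group (sample-size paragraph). The correlation r between entry support and vasopressor duration is not given. I assume 0.3 to 0.6, with 0.2 as a low case for what might remain after APACHE II. A linear model with no other covariates is used throughout.

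**1. The plan's own figure.** The article states: "Under the setting of alpha = .05 and power = 80%, the calculated sample size of each group is around 60". With n per arm = 2(z_alpha + z_beta)² × SD² / difference²:
- one-sided: 2 × (1.645 + 0.842)² × 42.25 / 9, giving 59, which reproduces it;
- two-sided: 2 × (1.960 + 0.842)² × 42.25 / 9, giving 74, which does not.

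Power at 60 per arm is 81.1% one-sided and 71.5% two-sided. Sidedness is a separate matter; both are carried only as reference values.

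**2. Size of a chance imbalance.** The standardised between-arm difference in a baseline variable has SE √(2/60) = 0.183 SD. The SE of the treatment difference is 6.5 × 0.183 = 1.19 h.

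**3. Shift in the estimated difference.** Shift = r × 6.5 h × imbalance. The imbalance needed to move the estimate by the full 3 h is 3 / (6.5r) SD, divided by 0.183 to express it in SEs.

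| r | 1-SE shift (h) | 1.96-SE shift (h) | Share of 3 h | Imbalance needed for 3 h |
|---|---|---|---|---|
| 0.2 | 0.24 | 0.47 | 16% | 2.31 SD = 12.6 SE |
| 0.3 | 0.36 | 0.70 | 23% | 1.54 SD = 8.4 SE |
| 0.5 | 0.59 | 1.16 | 39% | 0.92 SD = 5.1 SE |
| 0.6 | 0.71 | 1.40 | 47% | 0.77 SD = 4.2 SE |

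Even at r = 0.6, an imbalance of 4.2 SE has probability of about 0.000025.

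**4. What adjustment would recover.** The residual SD becomes 6.5 × √(1 − r²), so the gain in effective sample size is 1/(1 − r²).

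| r | 1/(1 − r²) | Two-sided power, 60 per arm | One-sided power | Two-sided n per arm |
|---|---|---|---|---|
| unadjusted | 1.00 | 71.5% | 81.1% | 74 |
| 0.2 | 1.04 | 73.2% | 82.5% | 71 |
| 0.3 | 1.10 | 75.5% | 84.3% | 68 |
| 0.5 | 1.33 | 83.1% | 89.9% | 56 |
| 0.6 | 1.56 | 88.5% | 93.5% | 48 |

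**5. If an unlucky allocation has occurred.** Given an adverse 1.96-SE imbalance, unadjusted two-sided power is 1 − Φ[(1.96 − (3/1.19 − 1.96r)) / √(1 − r²)]: 49%, 32% and 22% for r = 0.3, 0.5 and 0.6. Conditional type I error for an imbalance of that size is 8%, 13% and 16%. Averaged over all randomisations it remains nominal.

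**6. Agent.** If the two agents were used equally (assumed), the between-arm difference in their share has SE √(0.25 × 2/60) = 0.091. A gap of 10 points or more has probability of about 27%; one of 20 points or more, about 3%.

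**7. Is r in this range plausible?** The article does not say where the clock starts. If duration runs from infusion start and later duration does not depend on prior hours, entry times spread uniformly over 6 or 12 of the 24 permitted hours give prior hours an SD of 6/√12 = 1.73 or 12/√12 = 3.46 h. Then r = 1.73/6.5 = 0.27 or 3.46/6.5 = 0.53. Counting from randomisation removes this built-in part, leaving only whatever prognostic value prior hours have.

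**The case against.** - **Allocation is randomised, so this is not bias.** That stands. The shifts in step 3 are a component of the 1.19 h standard error, not an addition to it, and the log-rank test keeps its type I error.
- **Not listed is not the same as not recorded.** Largely right. The abstract presents its data items as examples, and a fuller case report form may exist. Applying the 24-hour rule requires the start time, and excluding patients on two or more vasopressors requires knowing what is being given. A reader might infer that the trial lacks all three items; the article does not support that. Only entry dose is neither listed nor implied.
- **The magnitude is assumed.** True. No r is given, APACHE II is already in the model, and what counts is the correlation left after it. The planned model is Cox, where adjustment does not shrink the standard error as in a linear model, so the gains in step 4 are indicative only.
- **The first analysis is untouched.** True: the log-rank test stays unadjusted, and only the second analysis gains.
- **The existing covariates are valid.** Also true. But the article names its adjustment set rather than leaving it open, and that set omits the predictors closest to this outcome. That part of the concern remains.

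**Conclusion.** The named Cox covariates omit the starting level of vasopressor support, although the primary outcome is time to stopping it and no stratification factor protects its balance. The consequence is lost precision and power. For an assumed r of 0.3 to 0.6, before allowing for APACHE II, the 95% range of chance shift is about ±0.7 to ±1.4 h against 3 h, and adjustment would be worth roughly 10% to 56% more patients on a linear scale.

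A reader might go further and infer that imbalance could hide or mimic the whole 3-hour effect. The article's own figures rule that out: it would take an imbalance of more than four standard errors even at r = 0.6. A shift of this size can tip a borderline result, no more. The point is a cheap improvement to a valid analysis.

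**What to change.** 1. Add three items to the data list, taken from the ICU chart: vasopressor agent, infusion rate at randomisation (weight-normalised), and hours from vasopressor start to randomisation. Show them in the baseline table.
2. Before unblinding, add entry dose (agent-specific) and hours since start to the pre-specified covariates of the Cox model, and state that time is counted from randomisation.
3. Leave the log-rank test unadjusted, and say so.

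Cost: minor chart abstraction, partly retrospective because the article says the trial is under way, and a few degrees of freedom. With two agents that is about four: one for agent, two for dose within agent, one for hours. They come on top of a model that already holds source of sepsis in four categories and several co-morbidities. Because deaths on vasopressor are censored, any such deaths would leave fewer than 120 events, so the coding of the covariates should be kept simple.

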## Discussion

Septic shock, usually caused by bacterial infection, is a severe systemic inflammatory consequence leading to multi-organ dysfunction. As with acute myocardial infarction, stroke and multiple trauma, treatment guidance for severe sepsis and septic shock in the initial period has been developed. Even though treatment recommendations are continually upgraded, mortality from sepsis and septic shock in the intensive care units is still high. Many remedies using herbal or traditional Chinese medicine have been proven to be potential adjuvant therapies in the treatment of sepsis and septic shock.

Si-Ni-Tang is composed of processed *Zingiber officinale*, *Glycyrrhiza uralensis*, and *Aconitum carmichaeli*. *Zingiber officinale *extract is found to have the ability to inhibit pro-inflammatory cytokines[3] and lipopolisaccharide-induced macrophage activation and function[4], and to reduce the bacterial load and suppress acute and chronic inflammation[5]. *Glycyrrhiza uralensis *extract is also considered to have anti-inflammatory properties and reduce lipopolysaccharide-induced pro-inflammatory cytokine secretion[6-8]. "Fuzi", the lateral root tuber of processed *Aconitum carmichaeli*, is used for treating pain, arthritis, cardiogenic shock, rheumatism, etc., in traditional Chinese medicine. Aconite roots are used only after processing and the procedure can hydrolyze aconite alkaloids into less toxic and non-toxic derivatives[9]. Aconite roots may contain coryneine chloride and higenamine, and possess vasopressor activity and positive chronotropic and inotropic effects[10,11]. Without a doubt, "Fuzi", *Aconitum carmichaeli*, is the critical factor in the remedy, Si-Ni-Tang.

Each component of Si-Ni-Tang is considered to be beneficial to septic shock patients, as described above. However, the most important theory of the Chinese medicine prescription is that there is a leading, coordinating, auxiliary and guiding effect in the remedy component. Perhaps, the exact benefit and effect of the drug combination go beyond what we already know. Only via conscientiously performed studies and positive outcomes can we push Chinese medicine onto the stage. And again, benefiting people and patients with septic shock is always the ultimate goal of our research. The clinical trial is being conducted now. If there are any conclusions in the near future, we would like to publish them later.

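### Censoring deaths on vasopressors makes the Kaplan-Meier curve and median overstate recovery, and leaves the primary comparison largely blind to extra deaths

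*Protocol article*

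**What the plan says.** The outcome paragraph of Methods/Design names the endpoints: "Shock reversal and time to cessation of vasopressor use would be the primary outcome measurements". The statistical paragraph that follows estimates the effect on time to cessation "from Kaplan-Meier curves and log-rank test for median time, and second, from adjusted Cox proportional hazards regression models for potential confounders" (age, baseline APACHE II, source of sepsis, co-morbidities). It then fixes the handling of death: "Patients who died before cessation of vasopressor use are treated as censored". It also states: "Analysis is performed on the intention to treat population". Patients who die on vasopressors are therefore in the analysis and leave it as censored observations.

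The data list includes "predicted mortality, ICU mortality, ICU length of stay, hospital mortality, hospital length of stay", but nothing links mortality to the time-to-event outcome. The Discussion says that "mortality from sepsis and septic shock in the intensive care units is still high". No death rate and no expected duration of vasopressor use is given. The article states no competing-risk method and no other way of counting deaths in this outcome.

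**The concern.** The Background asks whether the remedy shortens shock. A reader will take the Kaplan-Meier curve as the chance of being off vasopressors by a given time, and its median as the time by which half the patients are off. Both readings require that a patient removed by censoring would later have come off at the same rate as those still under observation. A patient who has died cannot.

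The comparison has a different problem. With deaths censored, the log-rank test and Cox model compare the rate of cessation among patients who are alive and still on vasopressors. A drug that left this rate unchanged but caused more deaths would lead to fewer patients recovering, and the test would show no difference. What is at stake is a primary result reported as unchanged shock duration while fewer patients in one arm came out of shock alive.

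**Working it through.** **Inputs from the protocol.** 120 patients, 60 per group, allocated 1:1. Treatment lasts up to 7 days, so 168 h is used as the horizon. The plan has no figure on death before cessation to reproduce. Its sample-size calculation uses a mean duration that "is 3 hours shorter than that of the placebo group, with a standard deviation of 6.5 hours", with no term for deaths.

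**Assumptions.** The share p of first events that are deaths is varied from 10% to 50%. Mean time to first event is 48 h, with constant hazards.

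**Step 1: curve and median.** Cessation hazard = (1 − p)/48; death hazard = p/48.

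- Kaplan-Meier, deaths censored: 1 − exp(−168(1 − p)/48)
- True cumulative incidence: (1 − p)(1 − exp(−168/48))
- Kaplan-Meier median: 48 ln 2/(1 − p)
- True median: −48 ln(1 − 0.5/(1 − p)), if reached

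At p = 0.30, Kaplan-Meier gives 1 − exp(−2.45) = 91%. The truth is 0.70 × (1 − exp(−3.5)) = 0.70 × 0.970 = 68%.

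| p | Kaplan-Meier, 7 days | True, 7 days | Kaplan-Meier median | True median |
|---|---|---|---|---|
| 10% | 96% | 87% | 37.0 h | 38.9 h |
| 20% | 94% | 78% | 41.6 h | 47.1 h |
| 30% | 91% | 68% | 47.5 h | 60.1 h |
| 40% | 88% | 58% | 55.5 h | 86.0 h |
| 50% | 83% | 48% | 66.5 h | never reached |

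Fixing the Kaplan-Meier median instead gives, at p = 0.30, an overstatement of 29 points (median 24 h), 23 points (48 h; 91.2% − 67.8%) or 17 points (72 h).

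The direction does not depend on constant hazards. Suppose that of 10 patients 3 die on vasopressors and 7 are weaned, the last to leave being weaned. Kaplan-Meier then ends at 100% off vasopressors; the truth is 7/10 = 70%.

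**Step 2: the comparison when the drug only adds deaths.** Simulation: 60 per arm, 4000 runs, two-sided 5% log-rank test, horizon 168 h, the same cessation hazard (ln 2/48 per h) in both arms. Deaths on vasopressors come to 19% on placebo and 39% on active; weaned by 7 days, 76% and 59%.

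- Deaths censored: mean z 0.01; 3.0% of trials significant for harm, 2.9% for benefit. This is the nominal 2.5% each way, within simulation error.
- Deaths kept as never ceased: mean z −1.62; 37.6% significant for harm, 0.0% for benefit.

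**Step 3: can the harmful arm look better?** Same size and test. Half the patients are sicker (cessation and death hazards both 0.25 of ln 2/48); the others have 1.5 and 0.02 of it. The drug multiplies only the death hazard.

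| Multiplier | Deaths, placebo vs active | Weaned, placebo vs active | Deaths censored: falsely favourable | Deaths kept: harm shown |
|---|---|---|---|---|
| 1 | 18% vs 18% | 66% vs 66% | 2.1% | 2.3% |
| 2 | 18% vs 29% | 66% vs 62% | 4.5% | 4.8% |
| 3 | 18% vs 36% | 66% vs 58% | 7.2% | 9.6% |
| 4 | 18% vs 41% | 66% vs 56% | 11.6% | 13.6% |

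With other assumed links between severity, weaning and death (deaths about 30% vs 43%, no effect on weaning), the hazard ratio with deaths censored was 1.01 to 1.02 and only 2.6 to 3.2% of trials were falsely favourable. With deaths kept, the hazard ratio was 0.75 to 0.84. Values above 1 favour the drug.

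**The case against.** The best defence is that censoring deaths is a recognised analysis. Log-rank and Cox do not need the premise that the dead would have been weaned later; they estimate and test the cause-specific hazard of cessation, which is a legitimate if partial answer to the question about shock duration. This stands, so the tests are not invalid. It does not rescue the curve and median, and a hazard among survivors on vasopressors says nothing about how many patients recover.

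A reader might go further and infer that a lethal drug would probably look beneficial. The documents do not support that. They give no death rate, no link between severity and weaning, and no expected harm. Step 3 shows a clear false advantage only under strong assumed harm, and almost none under other plausible links. The planned Cox adjustment for age and APACHE II works against this bias: in one simulation with deaths of 29% vs 41%, adjusting for a marker correlated 0.6 with severity moved the hazard ratio from 1.015 to 1.010, and full adjustment gave 0.99. Adjustment does not touch the unadjusted Kaplan-Meier and log-rank analysis, which is listed first.

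Other outcomes also offer some protection. Shock reversal is a primary outcome too, and a patient who dies on vasopressors does not meet its definition of at least 24 hours off norepinephrine or dopamine, although the article does not say how deaths count in it. ICU and hospital mortality are collected and would show gross harm. These soften the consequence without repairing the time-to-cessation analysis.

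An unseen analysis plan might add competing-risk methods. The point here is a rule that the article states, not something it leaves out.

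**Conclusion.** The concern holds in a limited form. Kaplan-Meier and its median overstate recovery whenever patients die on vasopressors. The direction is certain; the size is not. Under the assumed hazards the 7-day overstatement is 16 to 35 percentage points for death shares of 20 to 50% (94 − 78 and 83 − 48). The constant-hazard model is illustrative: its standard deviation equals its mean, so it does not match the 6.5 h in the sample-size sentence.

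The log-rank and Cox comparison is valid for the cause-specific hazard but largely blind to added deaths on vasopressors. A modest bias favouring the harmful arm is possible when severity drives both weaning and death. Its size rests on assumptions, and the planned adjustment reduces it.

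**What to change.** Replace the censoring sentence, before unblinding, with wording to this effect: Death before cessation is a competing event. Cumulative incidence of cessation by arm (Aalen-Johansen) replaces the Kaplan-Meier curve and median, and is shown beside the cumulative incidence of death on vasopressors. The primary comparison keeps patients who die as not ceased up to a fixed common day (for example Gray's test or a Fine-Gray model). The adjusted Cox model with deaths censored is supportive and is labelled a cause-specific hazard ratio.

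Gray's test or Fine-Gray is one choice. Vasopressor-free days with deaths scored zero would also count deaths as failures.

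The cost is wording and some programming; time of death on vasopressors is already needed for the present rule. The subdistribution hazard ratio is less familiar and mixes effects on weaning with effects on death, so both curves and the cause-specific result must be shown with it. The change does not make 120 patients enough to detect harm reliably: in Step 2, 37.6% of trials did so.

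### Post-hoc relative risks from Poisson regression will have over-wide confidence intervals unless a robust variance is used, and the post-hoc strata are not limited to baseline variables

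*Protocol article*

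**What the plan says.** All references are to Methods/Design in the protocol article. The outcome statement reads "Shock reversal and time to cessation of vasopressor use would be the primary outcome measurements". The treatment effect on time to cessation is estimated by Kaplan-Meier curves with a log-rank test, and then "from adjusted Cox proportional hazards regression models for potential confounders (age, APACHE II score at baseline, source of sepsis, co-morbidities".

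The next paragraph opens with "There is no planned subgroup analysis anticipated". It then makes an exception: "all of the variables which are found to be important predictors of shock reversal and adverse outcome will be used for stratifications for post-hoc analysis". A parenthesis gives the method: "relative risks will be estimated for the major outcomes using multivariate Poisson regression adjusting for covariates". No variance estimator is stated, and nothing limits the stratifying variables to those known at baseline.

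The data to be collected form a single list that mixes baseline items with outcomes and other items measured after randomisation. It includes "APACHE II score, predicted mortality, ICU mortality, ICU length of stay, hospital mortality, hospital length of stay, source of sepsis" and, at the end, "culture results (Gram-positive, Gram-negative or mixed) and duration of vasopressor infusion".

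**The concern.** There are two separate issues.

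**Variance.** A relative risk for shock reversal or death is a ratio of proportions. Poisson regression estimates that ratio validly, but its default variance treats each patient's 0/1 outcome as a count with variance p. The true variance is p(1-p). When the event is common, the default intervals are too wide. Poisson regression is the only method the article names for a relative risk on these outcomes, so a real difference in mortality, in either direction, could be reported as inconclusive.

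**Strata.** The rule is stated, not left open: variables found to predict outcome in this trial become the strata. Read literally, it admits length of stay and duration of vasopressor infusion. Shock reversal is itself defined by stopping norepinephrine or dopamine for at least 24 hours, so infusion duration is almost the outcome and would certainly emerge as a predictor. Treatment is meant to change that variable. Comparing the arms within its levels would no longer be a comparison of randomised groups.

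**Working it through.** **Inputs.** The planned enrolment of 60 per group comes from the sample-size paragraph of Methods/Design. The article gives no event risk and no expected relative risk, so there is no figure of its own to reproduce on this point. The event risks p below are assumptions, taken equal in both arms.

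**Formulas**, for an unadjusted comparison of two arms of size n:

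- binomial (correct) SE of log RR = sqrt[2(1-p)/(np)]
- model-based Poisson SE of log RR = sqrt[2/(np)]
- ratio of the two = 1/sqrt(1-p), which does not depend on n
- actual two-sided type I error at nominal 0.05 = 2[1 - Φ(1.96 × ratio)]

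**Worked case, n = 60, p = 0.6** (np = 36):

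- correct SE = sqrt(0.8/36) = 0.149; 95% limits are the estimate multiplied and divided by exp(1.96 × 0.149) = 1.34
- model-based Poisson SE = sqrt(2/36) = 0.236; the factor becomes exp(1.96 × 0.236) = 1.59
- ratio = 0.236/0.149 = 1.58

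**Range over assumed risks:**

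| p | SE ratio | Excess | Actual type I error |
|---|---|---|---|
| 0.2 | 1.12 | 12% | 0.028 |
| 0.3 | 1.20 | 20% | 0.019 |
| 0.5 | 1.41 | 41% | 0.006 |
| 0.6 | 1.58 | 58% | 0.002 |
| 0.7 | 1.83 | 83% | 0.0004 |
| 0.8 | 2.24 | 124% | below 0.0001 |

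**Simulation check.** For each risk, 2,000 trials of 60 per arm were simulated with no treatment effect and fitted by Poisson regression. At p = 0.3, 0.5 and 0.7, the model-based variance rejected in 0.013, 0.006 and 0.000 of trials. The sandwich variance rejected in 0.039, 0.050 and 0.044. The defect therefore lies in the variance and not in the Poisson model, and the robust option largely removes it.

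**Strata.** No arithmetic applies here; the passages can be set side by side. The Cox sentence names four covariates and ties APACHE II to baseline. The post-hoc sentence names none, gives no criterion for importance and carries no baseline restriction. The list of collected data contains at least three items fixed only after randomisation: ICU length of stay, hospital length of stay and vasopressor duration. The wording permits these as strata. It does not say that they will be used.

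**The case against.** The strongest reply on variance is that the article does not say the model-based variance will be used. Poisson regression with sandwich variance is a standard route to relative risks, and a condensed article may leave the estimator to the full protocol or analysis plan. This stands, and it makes the variance point conditional. A reader might infer that the intervals will be wrong; the text shows only that they will be wrong if the software default is kept.

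On strata, the list of collected data is not a list of candidate strata, and the covariates named elsewhere are sensible baseline ones. That also stands: use of post-randomisation variables is permitted, not announced. Further, choosing baseline variables because they predict outcome does not by itself bias the treatment comparison within strata. The bias argument applies only to variables measured after randomisation.

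Two stronger readings are tempting and are not supported.

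- A reader might see a contradiction between having no planned subgroup analysis and announcing stratified analyses. The second is introduced as an exception and labelled post-hoc, so the two statements are compatible.
- A reader might compute a high chance of a false positive, for example 1 - 0.95^14 = 0.51 for seven variables with two strata each. The article does not give those inputs: source of sepsis has four categories and culture results three, only variables found important would be used, and strata cut from the same 120 patients are not independent. Nor can the figure stand beside inflated standard errors. At p = 0.6 the error per test is about 0.002, and 1 - 0.998^14 is about 0.03.

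**Conclusion.** The concern holds in limited form. If the model-based Poisson variance is used, standard errors for relative risks of yes/no outcomes are too large by 1/sqrt(1-p): 20% to 83% for risks of 0.3 to 0.7. This rests on assumed event risks, equal risks in the two arms, an unadjusted comparison, and reading the major outcomes to include shock reversal and mortality. The error is conservative: it costs precision and can mask benefit or harm, but it does not create false positives. Separately, the stratification rule is driven by the trial's own outcomes and does not exclude post-randomisation variables; if these were used, the randomised comparison would be lost.

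The weight is minor to moderate. The analysis is labelled post-hoc, and the effect on time to cessation of vasopressors comes from the log-rank test and Cox model, which neither issue touches.

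**What to change.** - State that every relative risk for a yes/no outcome comes from Poisson regression with robust (sandwich) variance, or from a log-binomial model.
- Replace the rule that predictors found in the data define the strata. Limit post-hoc adjustment and stratification to the variables already named for the Cox model (age, baseline APACHE II, source of sepsis, co-morbidities), fixed before unblinding.
- If differences in effect between types of patient are to be shown, use treatment-by-covariate interactions on those variables and label them exploratory.

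The cost is one software option and a few sentences in the analysis plan. The downside is fewer exploratory tables.
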